# Efficacy of digital cognitive behavioural therapy for symptoms of generalised anxiety disorder: a study protocol for a randomised controlled trial

**DOI:** 10.1186/s13063-020-4230-6

**Published:** 2020-04-23

**Keywords:** Randomised controlled trial, RCT, Digital, Smartphone, Cognitive behavioural therapy, CBT, Generalised anxiety disorder, GAD, Anxiety

## Abstract

**Background:**

Generalised anxiety disorder (GAD) is a chronic and disabling condition with considerable personal and economic impact. Cognitive behavioural therapy (CBT) is a recommended psychological therapy for GAD; however, there are substantial barriers to accessing treatment. Digital CBT, in particular smartphone-delivered CBT, has the potential to improve accessibility and increase dissemination of CBT. Despite the emerging evidence of smartphone-based psychological interventions for reducing anxiety, effect size scores are typically smaller than in-person interventions, and there is a lack of research assessing the efficacy of smartphone-delivered digital interventions specifically for GAD.

**Methods:**

In the DeLTA trial (DigitaL Therapy for Anxiety), we plan to conduct a parallel-group superiority randomised controlled trial examining the efficacy of a novel smartphone-based digital CBT intervention for GAD compared to a waitlist control. We aim to recruit 242 adults (aged 18 years or above) with moderate-to-severe symptoms of GAD. This trial will be conducted entirely online and will involve assessments at baseline (week 0; immediately preceding randomisation), mid-intervention (week 3), post-intervention (week 6; primary end point) and follow-up (week 10). The primary objective is to evaluate the efficacy of the intervention on GAD symptom severity compared to a waitlist control at post-intervention. Secondary objectives are to examine between-group effects on GAD at follow-up, and to examine the following secondary outcomes at both post-intervention and follow-up: 1) worry; 2) depressive symptoms; 3) wellbeing; 4) quality of life; and 5) sleep difficulty.

**Discussion:**

This trial will report findings on the initial efficacy of a novel digital CBT intervention for GAD. Results have the potential to contribute towards the evidence base for digital CBT for GAD and increase the dissemination of CBT.

**Trial registration:**

ISRCTN, ISRCTN12765810. Registered on 11 January 2019.

## Background

Generalised anxiety disorder (GAD) is a chronic and disabling condition with a lifetime prevalence of 5–8% [1–3] and most patients continue to experience symptoms after 6 to 12 years [4]. GAD is characterised by excessive and persistent anxiety and worry that is difficult to control [5]. In addition to the considerable impact it has on the lives of individuals, GAD has serious economic consequences. It is associated with increased use of health care services, medical costs, absenteeism from work and decreased work productivity [6–8].

Cognitive behavioural therapy (CBT) is a recommended first-line treatment for GAD [9–12]. CBT for GAD encompasses a range of cognitive and behavioural components, including cognitive restructuring, imaginal exposure, situational (in vivo) exposure, stimulus control, applied relaxation, self-monitoring and psychoeducation [13–15]. Meta-analyses of randomised controlled trials (RCTs) show that, when compared to control conditions, CBT for GAD significantly improves anxiety, with large effect size scores [16, 17]. Despite this evidence base for CBT, availability is limited due to substantial barriers to accessing this treatment. These include insufficient numbers of trained therapists, costs, waiting lists, incompatible scheduling, distance from services and stigma [18, 19]. Digital CBT, or CBT delivered primarily via software applications on digital devices (e.g. computers, tablets, and smartphones) [20], provides a solution to help overcome treatment accessibility barriers and has the potential to increase dissemination of CBT. The importance of using digital technologies for improving mental health care is now well recognised [21] and there are a number of advantages offered by digital CBT. Digital CBT is cost effective [22, 23] scalable across people and geographies, and may reduce additional difficulties with attending appointments in person such as time constraints and stigma [18, 19]. Additionally, using algorithms, digital CBT has the potential to not only provide standardised and reliable, high-quality interventions for anyone, but can also be tailored to individual needs [20] thereby offering personalised psychological therapy.

The widespread uptake and use of smartphone technologies in our daily lives has increased interest in the use of these devices to deliver psychological therapies [24, 25]. In a survey of smartphone ownership conducted in 2019, 81% of US adults were found to own a smartphone [26] and smartphones are increasingly used by people to help address mental health problems [27]. They are therefore regarded as ‘next-generation’ platforms for delivering psychological therapies [21, 25], and the evidence base for the efficacy of smartphone-based interventions is growing. A recent systematic review and meta-analysis identified nine RCTs examining the effects of psychological therapies delivered primarily via smartphone on anxiety outcomes [28]. Findings showed that, compared to waitlist control conditions, smartphone interventions significantly reduced symptoms of anxiety, with a medium effect size. A more recent meta-analysis identified 29 RCTs examining the effects of smartphone interventions on generalised anxiety symptoms and found these to be superior to any control condition, with a small effect size [29].

Given that the effect size scores for in-person CBT for GAD are typically in the large range [17], there is clearly room for improvement in the efficacy of smartphone-based digital interventions. Furthermore, only four trials from the systematic review of Firth et al. [28] evaluated smartphone-based interventions designed to target anxiety. None of these four trials assessed efficacy for improving GAD symptoms, and only two of the four interventions were based on CBT, a recommended psychological therapy for GAD [9–12]. This is an important omission to address given the considerable personal and economic impact of GAD and the aforementioned difficulties associated with accessing CBT for GAD.

The current protocol is for a parallel-group superiority RCT examining the initial efficacy of a novel digital CBT intervention for GAD compared to a waitlist control for adults with at least moderate GAD symptom severity. The digital CBT intervention, Daylight, is fully automated (i.e. standalone functioning without human input) and is delivered entirely via a smartphone application (app). This form of digital CBT takes advantage of the wide uptake of smartphone devices and offers the fewest barriers to accessibility and greatest potential for scalability [20]. A waitlist control group comparison is appropriate to test the efficacy and safety of this new intervention in this population [30].

The primary objective is to evaluate the initial efficacy of a smartphone digital CBT intervention compared to waitlist control on self-reported GAD symptom severity at post-intervention (6 weeks from randomisation). Secondary objectives are to examine the effects compared to a waitlist control on GAD symptoms at follow-up (10 weeks from randomisation), and to examine effects on the following secondary outcomes at both post-intervention and follow-up: 1) worry; 2) depressive symptoms; 3) wellbeing; 4) participant-specific quality of life; and 5) sleep difficulty.

The primary hypothesis is that smartphone digital CBT intervention will be significantly more effective than waitlist control at treating GAD symptoms at post-intervention (6 weeks from randomisation). The secondary hypotheses are: 1) digital CBT will be significantly more effective than waitlist at improving GAD symptoms at follow-up (10 weeks from randomisation); 2) digital CBT will be significantly more effective than waitlist at improving the following outcomes at post-intervention (6 weeks from randomisation): worry, depressive symptoms, wellbeing, quality of life, and sleep difficulty; and 3) digital CBT will be significantly more effective than waitlist at improving the following outcomes at follow-up (10 weeks from randomisation): worry, depressive symptoms, wellbeing, quality of life, and sleep difficulty.

## Methods

### Design

This study is a parallel-group superiority RCT which will examine the efficacy of a novel smartphone-delivered digital CBT intervention for GAD compared to waitlist control for treating symptoms of GAD in adults with moderate-severe symptom severity. The DeLTA (DigitaL Therapy for Anxiety) trial will be conducted entirely online.

### Sample size

The sample size calculation was conducted using G*Power 3 [31]. The study aims to recruit 242 participants with GAD, with 121 participants randomised to each arm. This recruitment target accounts for approximately 30% attrition, based on the range of dropout rates from previous RCTs comparing smartphone-based digital interventions for anxiety to waitlist (19% to 45%; [32–34]). The sample size was determined based on an estimated medium effect on post-intervention scores on the seven-item Generalised Anxiety Disorder questionnaire (GAD-7) (Cohen’s *d* = 0.50) between the digital CBT and waitlist arms, with 90% power, a 1:1 allocation ratio, and with *α* set at 0.05. The effect size is based on a recent meta-analysis of RCTs of smartphone-delivered psychological treatment for anxiety versus waitlist which demonstrated a small-to-moderate (Hedges’ *g* = 0.33) between-group post-intervention effect on anxiety symptoms when compared to any active or waitlist/inactive control condition [28]. When comparing smartphone interventions with only waitlist/inactive control conditions, Hedges’ *g* increased to 0.45. The effect size of 0.50 corresponds to a minimally clinically significant 2-point change on the GAD-7 and a standard deviation of 4 in this population [35].

### Participants

For inclusion in this trial, participants must: 1) be aged 18 years or older; 2) score 10 or higher on the GAD-7 [35] indicating at least moderate GAD symptom severity; 3) screen positive for a GAD diagnosis on a digital version of the Mini-International Neuropsychiatric Interview (MINI) version 7 for DSM-5 [36], followed by telephone verification (see Procedure below for details); 4) be either not on prescription medication for anxiety, depressive symptoms, or poor sleep, or on a stable dose for at least 4 weeks; and 5) must not be currently receiving or have previously received CBT for anxiety in the last 12 months (this inclusion criterion was included after a modification was made by the ethical review committee after recruitment start). We will exclude participants who self-report: 1) being diagnosed with any of the following conditions: schizophrenia, psychosis, bipolar disorder, seizure disorder, substance use disorder; 2) having recent trauma to the head or brain damage; 3) having severe cognitive impairment; 4) having serious physical health concerns necessitating surgery or with a prognosis of less than 6 months; or 5) being pregnant. Individuals with other anxiety or related disorders (e.g. panic disorder, social anxiety disorder, and so forth) were included in the study as long as they endorsed worry (consistent with a GAD diagnosis) as their primary concern assessed at telephone screening.

Participants will be recruited online from the UK and the USA. A number of recruitment strategies will be used, including online, print, and broadcast media advertisements. Participants will receive 10 GBP in Amazon.com gift vouchers (or USD equivalent at the time of payment) in exchange for completing each of the core assessments following baseline (mid-intervention, post-intervention, and follow-up), and a bonus of 10 GBP (or USD equivalent) in vouchers for completing all assessments. Therefore, each participant can receive up to a total maximum of 40 GBP (or USD equivalent) in vouchers. Payment will be made at the end of the core study period for each participant (after 10 weeks from randomisation). If participants withdraw from the study, payment will be made for completion of any assessments at the point of withdrawal. Participants may withdraw themselves from the study for any reason at any time. The study investigator may also withdraw participants from the study to protect their safety and/or if they are unwilling or unable to comply with required study procedures after consultation with the study investigator team.

### Randomisation and allocation concealment

Participants will be assigned to the digital CBT or waitlist arm by blocked randomisation with a 1:1 allocation ratio. Randomisation will be carried out and the allocation sequence generated automatically upon completion of baseline measures using the randomisation function within Qualtrics Survey Software (Qualtrics, Provo, UT, USA, [37]). Members of the research team will be unable to influence randomisation and will be concealed from future assignments.

### Blinding

All assessments will be completed by participants online, independent from members of the research team, which will reduce the risk of bias associated with researcher-administered assessments. Participants will be informed of their randomly allocated condition (digital CBT or waitlist control) and will not be blind to group allocation. The trial coordinator will not be blind to group allocation as they will monitor uptake (download) of the intervention by participants. Participants who do not download the intervention will be reminded first by a daily email reminder for up to 3 days and then contacted by telephone. All other members of the research team will be blind to allocation. Participant contact with the trial coordinator will be limited to standardised emails containing instructions for completing online assessments and accessing digital CBT and will not cover treatment content or clinical support. Data analyses will be conducted by an independent external statistician who is not involved in the management of this trial. The statistician will be blind during the study and subgroup-unblind (groups labelled as ‘A’ and ‘B’) during the statistical analysis.

### Assessment points

Online assessments for the core study period will occur at 0 (baseline), 3 (mid-intervention), 6 (post-intervention) and 10 weeks (follow-up) from randomisation. Waitlist control participants will receive access to the digital CBT app after the follow-up assessment point (after 10 weeks from randomisation). In order to understand if effects persist over time, participants randomised to the intervention arm will also be invited to complete an optional longer-term uncontrolled assessment online at 6 months from randomisation without compensation. Table 1 presents details of the self-reported measures administered at each assessment point. After randomisation, participants will have up to 2 weeks to complete each questionnaire assessment battery. The trial coordinator will make every reasonable effort to follow the participant for the entire study period (from consent to the final follow-up assessment) using both email and telephone calls. To promote outcome data completeness, where necessary participants will be reminded to complete assessments first by a daily email reminder for up to 3 days and then by telephone for each overdue assessment. Participants who do not complete a study assessment will not be withdrawn from the study and will continue to be asked to complete any subsequent assessments. All online surveys will be hosted and stored on Qualtrics. Potential errors with data entry will be minimised as data will be entered by participants online.

**Table 1 Tab1:** Administered self-report measures and timeline

Measure	Screen	Study period			
		Baseline (week 0) and randomisation	Mid-intervention (week 3)	Post-intervention (week 6)	Follow-up (week 10)^**a**^
Basic screening questions (age, pregnancy)	X				
Medical and psychiatric history questions	X				
Prescription medication use	X				
MINI for GAD	X				
GAD-7	X		X	X	X
Demographic questions		X			
Credibility/expectancy questionnaire		X			
PHQ-9		X	X	X	X
PSWQ		X	X	X	X
SCI-8		X	X	X	X
WEMWBS		X		X	X
Patient-Generated Index		X		X	X
Modified symptom checklist				X	
Treatment satisfaction questions^b^				X	
Concomitant treatment		X	X	X	X

*GAD* generalised anxiety disorder, *GAD-7* seven-item Generalised Anxiety Disorder questionnaire, *MINI* Mini-International Neuropsychiatric Interview, *PHQ-9* nine-item Patient Health Questionnaire, *PSWQ* Penn State Worry Questionnaire, *SCI-8* eight-item Sleep Condition Indicator, *WEMWBS* Warwick–Edinburgh Mental Wellbeing Scale

^a^Participants randomised to the intervention arm will additionally be invited to complete a similar uncontrolled follow-up assessment online 6 months from randomisation

^b^Measure will be administered to participants in the intervention arm only

### Procedure

The Consolidated Standards of Reporting Trials (CONSORT; [38]) diagram displaying participant flow through the trial is shown in Fig. 1. Participants who respond to advertisements will be directed to the online participant information sheet and asked to consent to and complete an online screening survey as a first step in assessing eligibility against inclusion and exclusion criteria. Screening questions will assess age, GAD symptom severity (GAD-7), GAD diagnosis (MINI for GAD), medical and psychiatric history, prescription medication use and pregnancy. Eligible participants who meet inclusion criteria assessed above by the online screening survey will then be contacted by a member of the research team to take part in a brief 10-min telephone call. During this call, study procedures will be explained, any questions about the study will be answered, and we will verify participant reports of GAD against criteria from the Structured Clinical Interview for DSM-5 [39], ensuring that the participant feels their GAD symptoms are their current primary area of concern. All potential participants were informed (through study advertising, the participant information sheet and during the telephone conversation) that they should aim to use the app daily throughout the study period. Eligible participants who are willing to participate are then emailed a link to the online consent form.

**Fig. 1 Fig1:**
[figure not shown]
Summary of the trial design for the DigitaL Therapy for Anxiety (DeLTA) study. CBT cognitive behavioural therapy

Participants who consent will be allocated a unique identification code to use when completing all subsequent online surveys to ensure that identifiable information provided as part of consent is not directly linked to survey responses. This unique identification code will be used for data files to ensure confidentiality. Participants will receive an email asking them to complete an online baseline survey containing a battery of self-report measures (see Table 1). Upon completion of the baseline survey, participants will be automatically randomised to either the digital CBT or waitlist control condition and informed of their allocation by automated email. All participants allocated to digital CBT will receive immediate access to the intervention and access will not be withdrawn (i.e. participants are welcome to continue using the app after conclusion of their participation in the study). All waitlist control participants will be given access to digital CBT after the final controlled follow-up assessment point (after 10 weeks from randomisation).

### Digital CBT intervention

The intervention involves interactive and tailored delivery of digital CBT for worry and anxiety via a smartphone-based app, Daylight (https://www.bighealth.com/daylight). The app provides an interactive and media-rich experience and includes supportive visuals and brief animations. Daylight is a voice-led experience, in which a virtual therapist guides the user through intervention content. Throughout the intervention, participants are asked to complete questions within the app about their anxiety and other aspects of their experience (e.g. mood, sleep). Personalisation is built in using algorithms to tailor the intervention based on responses to questions and user’s progress.

Daylight was developed in collaboration with leading experts in the area of CBT for GAD and anxiety disorders. The content is based on evidence-based CBT techniques for the treatment of GAD, including psychoeducation, stimulus control, applied relaxation, cognitive restructuring, imaginal exposures and self-monitoring of progress. The programme is designed to be self-paced and includes four modules, each lasting up to 20 min, and shorter practice versions of the same techniques (lasting approximately 5 min). Modules are accessed sequentially, with access to a subsequent module available on completion of the previous module. The app provides feedback and troubleshooting based on the user’s feedback during the exercises as well as personalised recommendations for how the techniques may be applied in the user’s life. At the start of the programme, Daylight recommends that users aim to use the app daily to practice techniques; accordingly, the modules and practice exercises can be repeatedly accessed (as per the user’s preference) for reinforcement of specific techniques. Optional notifications in the form of emails (once weekly for the first few weeks of use), text messages (twice weekly) and in-app push notifications (of varied frequency) are used to prompt use of the app. The digital CBT intervention allows for monitoring of engagement through the automatic capture of objective usage statistics including the number of modules completed, frequency of access, and length of time taken to complete all modules.

### Measures

Outcomes are self-reported and measured online at screening or baseline (week 0; immediately preceding randomisation), mid-intervention (3 weeks), post-intervention (6 weeks) and follow-up (10 weeks). Measures included are indicated below and in Table 1.

#### Primary outcome

The primary outcome will be GAD symptom severity measured using the GAD-7 [35]. The GAD-7 will be administered at all time points. Items ask participants to indicate how often they have been bothered by symptoms over the last 2 weeks. Responses are given on a four-point Likert scale ranging from 0 (“not at all”) to 3 (“nearly every day”). Items are summed and total scores range from 0 to 21. The GAD-7 has been shown to have good validity and reliability, including internal consistency, test–retest reliability and construct validity [35].

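### The GAD-7 has no scheduled week-0 measurement, so its baseline is the screening score used for entry; this spares the between-arm difference but distorts within-arm change, reliable-remission rates and the mediation analysis

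*Protocol article*

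**What the plan says.** The Primary outcome section states: "The GAD-7 will be administered at all time points". The abstract lists "assessments at baseline (week 0; immediately preceding randomisation" as the first assessment, and Assessment points counts week 0 among the core assessments.

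Assessment points also says: "Table 1 presents details of the self-reported measures administered at each assessment point". In that table the GAD-7 is marked at Screen and at weeks 3, 6 and 10, and its cell for week 0 is empty. PHQ-9, PSWQ and SCI-8 show the reverse pattern: nothing at Screen, a mark at week 0.

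The Measures section is looser: "Outcomes are self-reported and measured online at screening or baseline (week 0; immediately preceding randomisation".

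The entry criterion under Participants is to "score 10 or higher on the GAD-7 [35] indicating at least moderate GAD symptom severity". Procedure places that test in the online screening survey: "Screening questions will assess age, GAD symptom severity (GAD-7), GAD diagnosis (MINI for GAD". A telephone call, emailed consent and the emailed baseline survey follow before randomisation.

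A GAD-7 baseline is then used in three places: as a fixed effect in the primary model (Statistical analysis), as the origin of the fall of at least 5 in reliable remission (Secondary outcomes), and as the start of GAD-7 change in the exploratory mediation analysis.

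**The concern.** If Table 1 is right, the primary outcome alone among the main symptom scales has no week-0 value, and its baseline is a score that admitted people because it was high. Scores selected in this way fall on average when repeated, without treatment. That fall would be counted as improvement.

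Four things are affected. Mean change within each arm is too large. The absolute rate of reliable remission is too high in each arm. Mediator change runs from week 0, while GAD-7 change runs from an earlier date. A score taken earlier, and cut off at 10, also predicts week 6 somewhat less well than a week-0 score would.

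**Working it through.** **1. The plan's own figure.** With a difference of 2, SD 4, two-sided alpha 0.05 and 90% power, n per arm = 2 × (1.960 + 1.282)² × (4/2)² = 84.1, so 85 (the t-test gives 85.03). Allowing for 30% attrition, 85/0.70 = 121.4, against the stated 121 per arm and 242 in total. The sample size reproduces and does not depend on this point.

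**2. Is the empty cell an artefact of reading the table?** No. The three neighbouring scales have Screen empty and week 0 marked, so the columns have not shifted. The words in Measures that allow screening or baseline agree with the table. The Primary outcome sentence does not, unless screening is taken to stand for week 0. For PSWQ, PHQ-9 and SCI-8 the same all-time-points wording goes with a real week-0 measurement.

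**3. Size of the selection effect.** The article gives no applicant mean, applicant SD or screening-to-week-0 correlation r. These are assumptions: mean μ 9, 11 or 13; SD 4.5 or 5; r from 0.6 to 0.9. Screening and week-0 scores are bivariate normal with no true change, rounded and limited to 0–21, and people are kept if screening is 10 or more.

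Ignoring the limit at 21, the expected fall is (1 − r) × SD × λ, where λ = φ(a)/(1 − Φ(a)) and a = (9.5 − μ)/SD.

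- μ = 9, SD = 5, r = 0.6: a = 0.10, λ = 0.863, fall = 0.4 × 5 × 0.863 = 1.73.
- μ = 13, SD = 4.5, r = 0.9: a = −0.78, λ = 0.377, fall = 0.1 × 4.5 × 0.377 = 0.17 (simulation 0.18).

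Simulated results:

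| μ | SD | r | Screening mean | Week-0 mean | Fall | Below 10 at week 0 | Below 10 and fall of 5 or more |
|---|---|---|---|---|---|---|---|
| 9 | 5 | 0.6 | 13.30 | 11.56 | 1.73 | 31.9% | 18.7% |
| 9 | 4.5 | 0.6 | 12.92 | 11.34 | 1.58 | 32.1% | 16.6% |
| 11 | 5 | 0.8 | 14.03 | 13.41 | 0.63 | 15.8% | 5.7% |
| 9 | 5 | 0.9 | 13.30 | 12.85 | 0.45 | 15.5% | 2.1% |
| 13 | 4.5 | 0.9 | 14.62 | 14.44 | 0.18 | 6.8% | 0.6% |

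Over the whole grid the fall is 0.18–1.73 points, 6.8–32.1% are below 10, and 0.6–18.7% already meet reliable remission. Of 121 per arm, that is 8 to 39 people below 10 (121 × 0.068; 121 × 0.321) and about 1 to 23 in reliable remission (121 × 0.006; 121 × 0.187). For scale, the protocol treats 2 points as the smallest clinically significant change.

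**4. Effect on the primary comparison.** In a simulated analysis of covariance (85 per arm, applicant mean 12, SD 4.5, r = 0.75), the screening covariate gave a mean estimate of −1.98 for a true −2 and a type I error of 0.047. The standard error was 0.578 with the screening score and 0.571 with a week-0 score, a ratio of 0.571/0.578 = 0.988; power was 0.926 against 0.932. Under other assumed correlations the week-0 covariate lowered the standard error by about 3–8%. The gain depends on how fast the correlation decays with time, which the article does not state.

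**5. Remission and reliable remission.** Remission is a later score below 10 and uses no baseline value, so a week-0 GAD-7 would change nobody's status at week 6 or 10. But the entry cut is the complement of the remission threshold. People already below 10 at randomisation who stay there therefore count as remitted. Reliable remission does use the origin, so there the choice of baseline alters the result.

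**The case against.** The Measures section openly allows screening or baseline, so using the screening score can be read as a disclosed choice, with one imprecise sentence under Primary outcome. That is partly right: the choice is hinted at. It is not stated, however, and the abstract and the Primary outcome section say otherwise.

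A reader might infer that the treatment effect on the GAD-7 is biased, or that the trial is underpowered. The documents do not support this. The screening score precedes randomisation and regression to the mean acts alike in both arms, so the adjusted contrast stays unbiased, and step 4 shows little or modest loss of precision. A reader might also infer that a week-0 score would correct the simple remission rates. It would not (step 5).

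The magnitude rests on assumed inputs and shrinks sharply at high correlation: at r = 0.9, with the same means and SDs, the fall is 0.18–0.45 points and 0.6–2.1% meet reliable remission. The GAD-7 covers the last 2 weeks, so a short gap would give overlapping windows and a high correlation. The further requirement for a positive diagnostic screen and telephone verification may also select persistent cases. Both caution against relying on the upper figures.

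The article states no maximum gap between screening and randomisation, but the full protocol may, so its absence is not a fault. The mediation analysis is exploratory, which limits the weight of that consequence.

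**Conclusion.** The concern holds with limited scope. As scheduled, the GAD-7 baseline is the screening score selected for being 10 or higher, and the text on timing contradicts Table 1. The between-arm difference, type I error and sample size are not affected.

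Within-arm change and the absolute reliable-remission rates are too high in both arms, and the simple remission rate includes people who may have been below 10 when randomised. Mediator and outcome change start on different dates, and the covariate loses some predictive value. The direction is certain for any screening-to-week-0 correlation below 1. The size is not: about 0.2–1.7 points, 7–32% below 10 at week 0, and 0.6–19% already in reliable remission, all on the assumptions in step 3. The change is worth making because it is cheap and concerns the primary outcome.

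**What to change.** Add the GAD-7 to the week-0 survey and mark the Baseline cell in Table 1. Use that score as the covariate and as the origin for change, reliable remission and mediation. Keep the screening score for eligibility only. Report the proportion below 10 at week 0, and keep those participants in the intention-to-treat analysis.

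The cost is seven items in an existing online survey and a small amendment. The real downside is that people already randomised have only the screening score (recruitment began on 2 August 2019 and was expected to end that November). Flag the source of the baseline in the model, and run a sensitivity analysis using the screening score for everyone.

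If recruitment has closed, the remedy is in the wording. State that baseline GAD-7 is the screening score, correct the sentence under Primary outcome, report the interval from screening to randomisation, and interpret change and remission only as contrasts between arms.
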